# ‘Relearning how to think’: A brief online intervention to modify biased interpretations in emotional disorders—study protocol for a randomised controlled trial

**DOI:** 10.1186/s13063-021-05459-3

**Published:** 2021-07-31

**Keywords:** Cognitive Bias Modification, Ambiguous interpretations, Emotional disorders

## Abstract

**Background:**

Cognitive biases play an important role in the development and maintenance of emotional disorders, such as depression and anxiety. Novel procedures, known as Cognitive Bias Modification (CBM), aim to reduce these dysfunctional information processing modes. This study develops a brief clinically based online intervention programme to modify biased interpretations in depression and anxiety (CBM-I_Clin_), overcoming some methodological issues that have been addressed in previous literature.

**Methods:**

Volunteer participants will be recruited via social media and posters at the university. They will be randomly assigned to an experimental group or a waiting list control group. Both groups will complete two assessment sessions (before and after the intervention) consisting of questionnaires measuring cognitive and emotional variables as well as experimental tasks measuring cognitive biases (i.e. attention, memory, and interpretation). After the first assessment session, only participants in the experimental group will receive a link to follow the four CBM-I_Clin_ sessions at home. All participants will receive, via email, follow-up questionnaires 2 weeks and 3 months after the second assessment.

**Discussion:**

This study will test the 'Relearning how to think', an online programme potentially beneficial to modify cognitive biases in emotional disorders. Several limitations of previous CBM procedures are addressed, and the impact of the programme both on objective cognitive bias tasks and clinical symptoms will be explored.

**Trial registration:**

ClinicalTrials.gov NCT03987477. Prospectively registered on June 17, 2019

## Background

Anxiety and mood disorders are the most common mental disorders in the general population, showing an 18.1% and 9.5% 12-month prevalence, respectively [1]. Both disorders are associated with high social and economic costs, as well as high rates of chronicity and relapse [2, 3].

High patterns of comorbidity between anxiety and mood disorders are consistent across studies [1, 4]. This comorbidity could be due, at least in part, to the fact that these disorders share transdiagnostic factors such as rumination [5] and are also likely to share some general risk factors [6]. Cognitive theories point to dysfunctional thinking as one of the main variables related to the onset and maintenance of these emotional disorders [6–8] According to these influential theories, depressed and anxious individuals show specific cognitive dysfunctions that can ultimately lead to symptom development [9, 10]. Several types of dysfunctions have been distinguished in regard to the onset and maintenance of emotional disorders. A useful heuristic to clarify diverse types of cognitive activity intervening in psychopathology is the so-called cognitive taxonomy, initially proposed by Ingram and Kendall [11]. This taxonomy differentiates between *structural* variables (i.e. broad cognitive schemas through which information is filtered, represented, and organised), *operational* variables (i.e. the mechanisms such as attentional, interpretation, or memory biases, by which cognitive structures work), and *product* variables (i.e. the tangible outputs such as thoughts, images, and memories, with which clinicians typically work with their clients). In general, cognitive biases have been defined as errors or distortions related to the operational domain that occur systematically at different times and across distinctive situations, reflecting ‘irrational’ modes of perceiving and elaborating information [12, 13].

### Cognitive Bias Modification

*Cognitive Bias Modification* (*CBM*) is a recent approach developed to alter cognitive biases and explore the link between them and symptom development. CBM procedures have mainly been aimed at modifying attentional, memory, or interpretation biases. Besides their clinical utility, these procedures are theoretically ambitious as their rationale is that a causal link between cognition and emotion would be demonstrated if changes in cognition are accompanied by consequent changes in emotion. Thus, the efficacy of CBM would provide support to the etiological role of cognition in emotional disorders. Although it has been applied in different conditions, such as eating disorders, substance abuse, or anger-related problems [14], the main focus has been on anxiety and depression [15–18].

Mathews and Mackintosh [19], in their pioneer study in the field of CBM for interpretation processes (CBM-I), used a paradigm to induce negative interpretation biases in healthy individuals and found a possible causal link to anxiety. Since then, studies using different training paradigms have found an association between change in interpretation bias and symptoms. Recent meta-analyses show evidence of a correlation between change in interpretation bias and negative mood [20], and significant differences between CBM training and control groups in anxiety and depression measures [17]. Some transdiagnostic factors, such as rumination, have also been found to improve with CBM-I [21]. A review of 12 meta-analyses of CBM procedures [18] revealed that there was a significant effect in 8 out of 10 meta-analyses for anxiety and 3 out of 7 meta-analyses for depression. Authors also found significant changes in attention biases in 8 out of 9 meta-analyses of studies using Attentional Bias Modification procedures (ABM) and changes in interpretation biases in the 3 meta-analyses on CBM-I. All this evidence reflects a possible causal link between cognitive biases and symptoms that, at least in the case of interpretation biases, might suggest the existence of a causal connection with a depressed mood in particular [22].

Although results are promising, there are some limitations in the current CBM procedures [23, 24]. First of all, some variables could affect the efficacy of CBM but remain unexplored. For example, although some studies are indicating that the use of mental imagery during CBM procedures could have a beneficial impact on CBM [25–27], it is still unclear whether this factor is relevant [17, 20]. Also, most CBM procedures are based on the idea that repetitive exposure to a specific way of processing information leads to its automatic use later in daily life [28]. Yet, the theoretical support to this mechanistic and repetitive procedure (that typically involves hundreds of trials) is still not clear. In fact, it could be possible that CBM procedures focused on enhancing elaborative rather than automatic processing modes could be more beneficial for disorders like depression where those elaborative mechanisms seem to be more affected than automatic ones [26].

Another methodological recommendation to improve CBM paradigms is the use of direct and indirect measures to evaluate cognitive change [14, 22]. This involves asking participants to directly respond to a series of interpretations (e.g. plausibility ranking or the scrambled sentence task) together with non-conscious measures of interpretations (e.g. reaction time). The evaluation of long-term benefits, when participants may have faced possible stressors in real life, has also been encouraged by previous research [29]. Also, cognitive biases at different processing levels (attention, interpretation, and memory) have traditionally been studied independently from each other but some authors now state the need to know how they interact with each other [30, 31].

### Objectives and hypotheses

The purpose of the study is to design a brief online intervention aimed at reducing the interpretation of negative emotional cognitive biases. The intervention will be applied to an experimental group to analyse its impact on cognitive and emotional variables in comparison to a waiting list control group. More specifically, the intervention is framed within the field of CBM-I but, instead of using repetitive training, it is based on the techniques frequently used in cognitive-behavioural therapies (e.g. [31–33, 34] Leahy). Thus, while original CBM studies (e.g. [19]) were designed to train participants to change automatic processing of information with repetition of trials, the current intervention aims to teach participants the meaning and consequences of emotional cognitive biases, and how to modify them.

This study also aims to address some limitations of previous CBM procedures. First, based on previous evidence [35], mental imagery is used in order to shed some light on its role when modifying cognitive processes. Second, direct and indirect measures of cognitive performance are used to complement the information provided by self-report questionnaires. Moreover, these measures evaluate the three different domains proven to be most affected in emotional disorders (attention, interpretation, and memory) [36], given the need to explore their interplay [37]. Finally, a longitudinal follow-up was used to explore the continuation of benefits in time.

It is hypothesised that there will be a significant change in interpretation bias (less negative or more positive/neutral) from pre-intervention to post-intervention in the experimental group in comparison to the control group. It is also expected that changes in interpretation biases will also be associated with significant changes in attention and memory biases (less negative or more positive/neutral) from pre-intervention to post-intervention in the experimental group in comparison to the control group. Finally, it is hypothesised that the intervention will help the experimental group to reduce symptoms of depression and anxiety and increase well-being from pre-intervention to post-intervention in comparison to the control group. Due to the lack of conclusive findings from previous studies, it is explored whether these changes are maintained over time (after 2 weeks and 3 months) and the temporal dynamics of the different cognitive bias processes (attention, interpretation, and memory).

## Methods

### Participants and recruitment

Participants will be volunteer students from the Complutense University of Madrid who will be recruited via social media channels associated with the university and posters at the Faculty of Psychology. Inclusion criteria will be (1) aged 18 years or older and (2) being interested in the intervention, announced as a free online programme to ‘learn how to control the influence of thoughts on emotional reactions’. The announcement will include the name and email address of one of the researchers. Volunteers will be instructed to contact the researcher for more information, and academic course credits will be offered to those interested within the context of an official faculty programme that aims to promote the students’ involvement in academic training events. Exclusion criteria will include (1) having any form of visual and/or auditory disability that makes participants unable to follow online sessions and (2) lack of Internet access. No restrictions will be placed regarding concomitant treatment during the study, although this information will be monitored during the assessment sessions. When participants first contact the researcher, they will be explained all the details of the intervention and procedure. Inclusion and exclusion criteria will be evaluated by asking about their ability to correctly complete the programme (i.e. no disabilities and Internet access). The information about the intervention will also be given during their first visit to the laboratory in a printed document format before they are asked to sign the consent form.

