### Analytic plan

Demographic data and pre-treatment measures will be analysed to test for group differences with analysis of variance and chi-squared test for nominal variables.

Complete case analyses will be conducted for those participants who complete all 4 online sessions and attend pre- and post-assessment evaluation sessions. A series of 2 (group: experimental, control) × 3 (symptom group: never, present, past) × 2 (time: pre-training, post-training) analyses of variance will be performed to evaluate the change between groups. The symptom group will be created based on present and past symptoms of depression and/or anxiety to explore their influence on the results. Intention-to-treat (ITT) analyses will be conducted with all participants, regardless of session or outcome measure completion. ITT mixed models (restricted maximum likelihood (REML) estimation) will be used to account for missing data [71]. Binary logistic regression will be used to evaluate the assumption that data is Missing at Random (MAR). Exploratory mediation analyses will be conducted to study the interplay between the different cognitive bias scores given the change of the intervention. Finally, follow-up assessments will be included in a series of analyses of variance to evaluate group differences in time. All analyses will be performed in SPSS Statistics 20 with an *α* level of 0.05.

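### Entry requires no symptoms, so the whole-sample comparison supports conclusions about unselected students, not about people with emotional disorders

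*Protocol article*

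**What the plan says.** **Framing.** The title places the programme in emotional disorders. The Abstract (Background) describes an "online intervention programme to modify biased interpretations in depression and anxiety", and the Abstract (Discussion) calls it "an online programme potentially beneficial to modify cognitive biases in emotional disorders". Objectives and hypotheses states, as a hypothesis against the control group, that "the intervention will help the experimental group to reduce symptoms of depression and anxiety".

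**Entry.** Under Participants and recruitment, "Participants will be volunteer students from the Complutense University of Madrid". The criteria are: "Inclusion criteria will be (1) aged 18 years or older and (2) being interested in the intervention". The exclusions are sensory disability that prevents following the sessions and lack of Internet access. Screening checks only these practical points.

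**Use of symptom status.** PHQ-9 and GAD-7 are completed before the intervention, each with a cutoff of 10 or more, in order to classify participants. The Analytic plan enters a three-level factor (never, present, past) in a 2 × 3 × 2 analysis of variance, with this purpose: "The symptom group will be created based on present and past symptoms of depression and/or anxiety to explore their influence on the results".

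**Sizing.** Sample size uses d = 0.43 for interpretation bias in a design with two groups and two time points. This gives 73 participants, raised to 88 for attrition. It has no symptom factor, symptom effect size or assumed symptomatic share.

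**The concern.** The population named in the claim is not the population that entry selects. The plan's own never and past categories show that entrants without current symptoms are expected. The whole-sample group-by-time contrast therefore estimates an effect averaged over students with and without symptoms, in a mix that nobody has fixed.

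This could mislead in two ways. A positive interpretation-bias result could be carried over to clinical populations that the trial did not select. A null symptom result could be reported as no effect in emotional disorders, although it is a result for a mixed student sample. The contrast that does bear on disorders, the one within participants with present symptoms, is labelled exploratory and was not sized.

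**Working it through.** **1. Reproduce the plan's figure.** Inputs from Sample size: d = 0.43, two-sided α = 0.05, power 0.95, two groups, two time points. The correlation between time points is not stated, so 0.5 is assumed. For the group-by-time interaction in the G*Power parameterisation:

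- f = d/2 = 0.215
- noncentrality λ = f² × N × m / (1 − ρ), with m = 2 and degrees of freedom 1 and N − 2
- N = 73: λ = 0.046225 × 73 × 2 / 0.5 = 13.50, power 0.952
- N = 72: power 0.949

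The stated 73 is reproduced. For attrition, 73 × 1.2 = 87.6, which rounds up to 88. The 0.95 therefore belongs to interpretation bias in all completers.

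**2. Power in the present-symptom subset.** The article gives no symptomatic share, so a range is assumed. The same f and ρ are applied to share × 73.

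| Assumed share | Symptomatic completers, both arms | Power in subset |
|---|---|---|
| 20% | 14.6 (about 15) | 0.33 |
| 25% | 18.3 | 0.41 |
| One third | 24.3 | 0.53 |
| 50% | 36.5 (about 37) | 0.71 |
| 75% | 54.8 | 0.88 |

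All of these fall below 0.95. Applying f = 0.215 to symptoms is only illustrative, because the article gives no symptom effect size. The value is also generous: in this parameterisation f = 0.215 means a between-arm difference in change of 4 × 0.215 = 0.86 SD. If 0.43 SD is the difference in change, then f = 0.1075, and subset power is 0.12 at a 20% share and 0.24 at 50%. That is a separate question about the sizing.

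**3. Precision in the subset.** The 95% half-width for a difference in mean change, in SDs of change, is t × √(1/n₁ + 1/n₂).

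- 15 people split 7 and 8: 2.160 × √(1/7 + 1/8) = 2.160 × 0.518 = 1.12
- 37 people split 18 and 19: 2.030 × √(1/18 + 1/19) = 2.030 × 0.329 = 0.67

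**4. The classifier.** Patient Health Questionnaire-9 describes nine items, each scored 1 to 4, added up, with a cutoff of 10 or more. As written the minimum total is 9 × 1 = 9. One item rated a single step above the lowest answer already gives 10 and meets the cutoff. The present and past groups cannot carry a contrast until item scoring and cutoff are reconciled.

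**The case against.** The other side has real points. Interpretation bias is the stated purpose, the first hypothesis and the only basis for sizing. It is a continuous outcome measurable in every entrant, so the trial can answer its main question. The student population is stated openly. The Abstract says the impact on bias tasks and clinical symptoms will be explored, and Randomisation and blinding justifies the waiting list as giving a first impression. Symptom group is a baseline factor in the planned model, so the three-way interaction is already tested. Open entry with a symptom moderator is a legitimate design. All of this stands. It leaves the mismatch between the disorder-level wording and the sample, the symptom reduction stated as a hypothesis, and the merely exploratory status of the contrast that matters for disorders.

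A reader might infer more than the documents support:

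- **That most entrants have nothing to reduce, so few can answer the question.** The Background gives prevalences, "showing an 18.1% and 9.5% 12-month prevalence, respectively". Applied to 88 people, 18.1% (full overlap) to 27.6% (18.1 + 9.5, no overlap) would be 16 to 24. But these are 12-month disorder prevalences in the general population, whereas the present group is defined by questionnaire scores in volunteers drawn by an advert about thoughts and emotional reactions. The share could be higher.
- **That never-symptomatic students sit at the floor of DASS-21, or cannot benefit.** No DASS-21 distribution is given. It is a summed score that can fall from sub-threshold levels.
- **That allocation ignores symptom status.** The article mentions an Excel macro and a random sequence. It does not say whether the sequence is simple, blocked or stratified, and an article may leave that to the full protocol.
- **That the whole-sample symptom result is no evidence at all.** It is the valid result for unselected students.

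**Conclusion.** The point holds as one about scope. Framing and symptom hypothesis refer to emotional disorders, while entry is open to any interested adult student who can follow the programme. The whole-sample contrast therefore supports conclusions about self-referred students not selected for symptoms. The interpretation-bias hypothesis remains answerable in all of them.

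For a disorder-level statement the relevant contrast is the one among participants with present symptoms. At an assumed share of 20% to 50% its power is about 0.33 to 0.71, with 95% half-widths of roughly 1.1 to 0.7 SD of change. These figures rest on an assumed share, an assumed correlation of 0.5 and an effect size borrowed from interpretation bias. That entry does not require symptoms rests on none of them.

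**What to change.** 1. In the title, the Abstract (Discussion), Objectives and hypotheses and the conclusions, describe the population as self-referred university students not selected for symptoms. Limit the whole-sample conclusion to them.
2. Pre-specify the group-by-time contrast within participants with present symptoms, from the planned 2 × 3 × 2 model and from the intention-to-treat mixed model. Report it with its confidence interval as the basis for any statement about emotional disorders. Keep the whole-sample symptom result as the result for unselected students. Trial status reports the study complete by December 30, 2020. If outcomes have already been examined, say so and label the contrast post hoc.
3. Before step 2, reconcile the PHQ-9 item scoring with the cutoff, so that the present and past groups are defined.
4. Secondary: state whether allocation was stratified. If it was not, present-symptom status is measured before the programme link is sent and could serve as a stratum in a follow-on trial. The gain is small. For example, an 11:5 split instead of 8:8 raises the standard error by about 8% (√(1/11 + 1/5) = 0.539 against √(2/8) = 0.500), and chance imbalance does not bias the contrast.

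The cost is wording and one named contrast, with no extra participants. The downside is a narrower headline claim and a wide interval for the symptomatic contrast.

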### Randomisation and blinding

This study is a randomised superiority trial with two parallel groups and a 1:1 allocation ratio. Participants will be randomly allocated to the experimental group (CBM_Clin_) or a control waiting list group. This control group was chosen due to the novelty of the intervention, for which a waiting list is recommended to get a first impression of its effects [38]. Randomisation will be conducted by the main investigator using an Excel macro. This method assigns a different code to each group, which will only be known by the researchers. In this trial, solely participants will be blinded to their allocation and the meaning of codes.

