#### Patient Health Questionnaire-9

The PHQ-9 [56] is a 9-item self-report questionnaire to assess any present episodes of depression according to the DSM-IV diagnostic criteria. Each item is rated in frequency on a 4-point scale from 1 (not at all) to 4 (nearly every day). This questionnaire has shown good reliability with a Cronbach’s *α* of 0.89 [57]. An adapted PHQ-9 will also be used to measure past episodes of depression. The method of aggregation will consist in adding up the values of each item. In this study, the standard diagnostic cutoff score of PHQ-9 ≥ 10 [58] will be used to create groups based on present and past episodes of depression. This questionnaire will be completed online at pre-intervention to classify participants according to their symptom levels.

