### Procedure

Figure 4 shows the schedule of enrolment, intervention, and assessment following the recommendations for clinical trials [70]. The main investigator will create a random sequence to assign participants to either the experimental or the control group. After the volunteers contact the main researcher for initial information about the study, they will receive a phone call from the researcher to explain the procedure of the study and the outline of the intervention programme. Participants will be given all the ethical considerations regarding their participation and will be allowed to ask any further questions. After they verbally consent to continue, they will be assigned a participation code, randomly generated to ensure anonymity. Then, participants will complete two different assessments. First, they will receive the questionnaires for the first assessment (i.e. PHQ-9, GAD-7, AST-D-II, DASS-21, DAS, RRS, PHI, and CEQ), together with the information sheet providing details of the programme. Questionnaires will be completed online, using the Qualtrics platform, to which participants will be invited via a personalised link sent to their mailbox. Second, the day after participants complete these questionnaires at home, they will attend the first session in the lab. At that moment, they will be given the consent form (explaining their right to freely withdraw from the study at any moment) and will be asked to sign it if they agree to continue. Then, the main investigator will explain in detail the rationale of the intervention ‘Relearning how to think’ and will answer any questions from the participants. If they finally agree to participate, they will be asked to sign the consent form and complete some demographic information. Then, the three experimental tasks (MCAT, computerised beads task, and recall task) will be administered.

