**Fig. 4 Fig4:**
[figure not shown]
Schedule of enrolment, interventions, and assessments

After completion of the three lab tasks, participants in the experimental group will receive in their email the link to complete the online programme from home. They will need to log in to an online platform created for this study and will be invited to create their own account and password to access the materials. Information will be stored solely using the participant’s code number and only the main researchers will have access to the data. These data will be recorded in the database of the platform and will be used by the researchers to monitor if participants in the experimental group complete all four online sessions before the post-intervention evaluation. When participants first access the platform, they will find only the first session available. Access to the next session will be granted only 24 h after completing the previous one. This intermission between sessions aims to enhance participants’ processing of the contents of each session as well as to avoid cognitive overload and boredom.

After finishing the 4-session training programme, participants in the experimental group will be notified again, after approximately 10 days, for a second assessment session. The control group will be allowed to complete the intervention right after the second assessment. To improve adherence, both groups will receive a reminder for the second assessment session the day before. Finally, participants will be sent the follow-up questionnaires (AST-D-II, DASS-21, PHI, SE) twice (in the next 2 weeks and 3 months). To increase adherence during the follow-ups, participants will be sent up to a maximum of three reminders to complete questionnaires. Both groups will have the opportunity to complete a ‘feedback question’ to give their opinion about the intervention. This question will be included in the post-assessment for the experimental group and at the follow-ups for the control group.

The procedure has been approved by the university ethics committee (Ref. 2018/19-017) and has been registered (ClinicalTrials.gov NCT03987477). Moreover, it follows the recommendations for a clinical trial protocol [70].

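### Allocation is described without balancing on symptom group, although that class is measured before the arms diverge and is used in the analysis; stratifying would be a cheap gain in precision

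*Protocol article*

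**What the plan says.** The Randomisation and blinding section calls this a "randomised superiority trial with two parallel groups and a 1:1 allocation ratio" and adds that "Randomisation will be conducted by the main investigator using an Excel macro". The Procedure section says that "The main investigator will create a random sequence to assign participants to either the experimental or the control group". Neither place mentions strata, blocks or minimisation.

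The PHQ-9 section says of that questionnaire: "This questionnaire will be completed online at pre-intervention to classify participants according to their symptom levels". The GAD-7 section uses the same sentence. On timing, the Procedure section states that "the day after participants complete these questionnaires at home, they will attend the first session in the lab", and the text after Fig. 4 that "After completion of the three lab tasks, participants in the experimental group will receive in their email the link to complete the online programme".

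The Analytic plan crosses arm, a three-level symptom factor (never, present, past) and time in a complete-case ANOVA. It explains: "The symptom group will be created based on present and past symptoms of depression and/or anxiety to explore their influence on the results". The intention-to-treat mixed models and the follow-up analyses of variance are then described without that factor.

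**The concern.** Entry is open to any interested adult student with no symptom criterion (Participants and recruitment), so the sizes of the never, present and past groups are left to whoever volunteers. Symptom level is plausibly prognostic for the depression, anxiety and bias outcomes. The plan measures it before the arms diverge and analyses by it, but the allocation as described does nothing to balance the arms within it.

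Two things are at stake. The first is the precision of the arm comparison within a small symptom group, and so of the arm-by-symptom comparisons that the ANOVA is meant to explore. The second is balance on symptom level in the models that are described without symptom group.

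**Working it through.** **The plan's own figure.** For the group-by-time test in a 2 x 2 repeated-measures design, f = 0.43/2 = 0.215 and lambda = N x f^2 x 2/(1 - rho). With N = 73 and rho = 0.5 (assumed; not stated), lambda = 73 x 0.046225 x 4 = 13.5 and power is 0.952, so 73 is reproduced. Then 73 x 1.20 = 87.6, rounded to 88. This calculation covers two groups and two times, without symptom group. The present point does not change it.

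**Order of events.** Online questionnaires, including PHQ-9 and GAD-7; lab visit the next day; three lab tasks; programme link to the experimental arm. The classification data are therefore in hand before treatment differs. The article does not say when the random sequence is made or applied relative to the questionnaires.

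**Cell sizes.** Two arms by three symptom groups make six cells: 88/6 = 14.7 on average, or 73/6 = 12.2 at the minimum sample size.

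**Chance of an uneven split.** For a stratum of size s, the number X in one arm is binomial(s, 0.5) under unrestricted randomisation, or hypergeometric if arm totals are held at 44/44. The probability that max(X, s - X)/s reaches a threshold is below. Stratum sizes are assumptions.

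| Stratum size | 70/30 or worse: unrestricted | 70/30 or worse: totals 44/44 | 80/20 or worse: unrestricted | 80/20 or worse: totals 44/44 |
|---|---|---|---|---|
| 10 | 34% | 31% | 11% | 9% |
| 15 | 12% | 9% | 3.5% | 2.1% |
| 20 | 12% | 7% | 1.2% | 0.4% |
| 29 (near-equal thirds) | 2.4% | 0.6% | <0.1% | <0.1% |

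For example, at s = 10: 2 x (120 + 45 + 10 + 1)/1024 = 352/1024 = 34%. Counts are whole numbers, so the probabilities do not fall smoothly with size; at s = 19 the 70/30 figures are 6.4% and 3.6%.

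Chance that at least one of three strata is split 70/30 or worse, unrestricted (totals 44/44), by simulation:
- 30/29/29: 9% (2%)
- 44/29/15: 15% (9%)
- 53/26/9: 20% (16%)
- 58/20/10: 42% (37%)

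**Cost within a stratum.** If a share p goes to one arm, the variance of that stratum's arm contrast is multiplied by 0.25/(p(1 - p)): 1.10 at 65/35, 1.19 at 70/30, 1.56 at 80/20.

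**Cost to the overall contrast adjusted for symptom group.** Information relative to perfect balance is the sum over strata of k(s - k)/s, divided by N/4, where k is the number in one arm. Its expectation does not depend on the stratum sizes:
- Unrestricted: (88 - 3)/88 = 0.966.
- Totals 44/44: 85 x [44 x 44/(88 x 87)]/22 = 0.977.

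The average loss is thus 2-3%. The simulated 5th percentile is about 0.91 (0.93 with totals fixed).

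**Models without symptom group.** If 35% of participants were in the present group (assumed), the arm difference in that share would have standard deviation sqrt(2 x 0.35 x 0.65/44) = 0.102, a 95% range of about +/-20 percentage points.

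**The case against.** The strongest reply is that this is a preference and not an error. Unstratified randomisation is unbiased, and chance imbalance is already reflected in the standard errors. The complete-case ANOVA contains symptom group and each participant's baseline, and the symptom comparisons are labelled exploratory. The hypotheses and the sample size concern arm by time only. All of this stands, and it limits the point to precision.

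Small blocks within strata could also make assignments easier to foresee. The main investigator creates the sequence and also explains the programme at the lab visit, and only participants are blinded. That stands too, but avoiding blocks of 2 and concealing the lists answers it.

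Some stronger readings are tempting, and the document does not support them:
- A reader might infer that one sequence for everybody is drawn before any questionnaire, or that stratification was ruled out. The Procedure section says only that a random sequence will be created. Timing is not fixed, and a condensed article's silence is not an exclusion.
- A reader might infer that cells could end up nearly empty. The chance that either arm receives two or fewer is 422/1,048,576 = 0.04% for a stratum of 20 and 158/4096 = 3.9% for 12. It reaches 112/1024 = 11% only at 10, where even perfect balance gives five per arm.
- A reader might infer that the arm comparison is confounded. The stated ANOVA adjusts for symptom group, and nothing in the document shows that symptom level predicts dropout.

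**Conclusion.** The point holds as a cheap improvement to the design, not as a threat to validity. The allocation as described balances nothing on a factor that the plan itself measures in time and analyses by. The average price is small for the overall adjusted contrast (2-3% of information). It can be material for one stratum if that stratum is small: 7-34% chance of a 70/30 or worse split at sizes 10, 15 and 20, with variance multiplied by 1.19 or more. If the groups are near-equal thirds the risk is 0.6-2.4% per stratum and hardly matters.

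The conclusion rests on stratum sizes that the document does not give. It also takes the article's description of allocation, and of the intention-to-treat and follow-up models, as complete on this point.

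**What to change.** For the design:
- State one rule that places each participant in never, past or present. The Analytic plan combines depression and/or anxiety without saying where someone with both a past and a present episode belongs. The PHQ-9 section scores nine items from 1 to 4 (minimum sum 9) beside a cutoff of 10 or more, which should be reconciled.
- Score both questionnaires when the online battery is returned.
- Allocate after the baseline lab tasks, from three 1:1 permuted-block lists with varying block sizes larger than 2, concealed from the person who enrols. If assignment now happens earlier, it must move to this point.
- Keep symptom group in the ANOVA and add it to the intention-to-treat and follow-up models.

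The cost is three lists in place of one and prompt scoring of two questionnaires. An unfinished block of size b leaves an imbalance of at most b/2 in its stratum (2 for a block of 4), so overall arm sizes may differ slightly. Predictability rises somewhat if the lists are not concealed.

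Trial status reports the study as completed by 30 December 2020, so allocation can no longer be changed. What remains is to state how and when allocation was done and whether it was stratified, report the six arm-by-symptom counts, add symptom group to the intention-to-treat and follow-up models, and present the symptom comparisons as exploratory and open to chance imbalance.
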